#### Primary outcomes

The primary outcome is the feasibility of conducting a full-scale RCT. Feasibility will be assessed by evaluating the following outcomes.
Willingness of participants to enroll in the study (from recruitment database).Number of eligible volunteers (from recruitment database).Recruitment rate (from recruitment database).Adherence with allocated intervention and log book completion (from Study Practitioner notes, and participant log book).Adverse events (from Study Practitioner notes, adverse events database and participant log book).Success of blinding (risk of performance and detection bias) (from *Credibility and Expectancy Questionnaire*).Drop-out rate (from trial database).

The following parameters were set to inform feasibility: (i) a recruitment rate of 1 participant per week; (ii) minimum adherence with shoe insert wear of 2 h per day, 5 days a week; and (iii) a drop-out rate of ≤20%.

Credibility and the participant’s expectations of treatment will be evaluated using the Credibility and Expectancy Questionnaire [24]. This will be completed at baseline, and at the participant’s second visit with the study physiotherapist (~ 2 weeks post-randomisation). The Credibility and Expectancy Questionnaire consists of six items organised into two sections; four items related to thoughts, and two items related to feelings. A subsequent study determined that credibility is derived from the first three thought items, and expectancy derived from the fourth thought question and the two feeling questions [25]. The Credibility and Expectancy Questionnaire has been administered in adolescent populations in previous studies [26, 27].

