**Fig. 1 Fig1:**
[figure not shown]
Participant flow through the study

Participants will be randomised to one of two interventions: (i) prefabricated contoured foot orthoses, or (ii) flat shoe insoles. Randomisation procedures will be via concealed allocation, with the randomisation sequence held by an offsite investigator ([name]). Due to the nature of the two shoe insert interventions (contoured vs. flat inserts), it is not possible for study physiotherapists to be blinded to group allocation. Primary outcomes for feasibility will be collected by a blinded assessor ([name]). Secondary outcomes will be self-reported by participants, who are considered assessors. To facilitate blinding of participants (and therefore assessors of secondary outcomes) via limited disclosure, participants will be informed that they will be randomised to one of two shoe insert interventions, and will not be informed of the differences between the two inserts or the study hypotheses [12, 20].

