### Outcome assessment

At baseline, demographic and PFP data including age, sex, weight, height, affected knee, bilaterality of PFP, symptom duration, and aggravating activities will be collected. Participants will complete patient-reported outcome measures at baseline, and at 6 weeks and 3 months post-randomisation. Data collection will largely be completed via an online platform (REDCap), but participants will have the option to complete a paper version. For the study duration, participants will be asked to keep a daily log (assisted by their parent/guardian as required) of: activities or sport completed each day, knee pain severity (rated on a 10-point numerical rating scale; 0 = no pain, 10 = worst pain imaginable), type of shoes worn that day, hours spent wearing the footwear and shoe inserts, adverse effects associated with the shoe inserts, medication use, and any other comments (see Additional file 2). Study physiotherapists will record attendance, prescription notes and adverse events during fitting and follow-up. The primary endpoint is 3 months.

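### The primary feasibility outcome of blinding success rests only on a questionnaire that measures credibility and expectancy, last completed at about 2 weeks

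*Protocol article*

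**What the plan says.** All references are to the protocol article.

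- **Outcome and source.** The Primary outcomes section lists "Success of blinding (risk of performance and detection bias" as one of seven feasibility outcomes. The Credibility and Expectancy Questionnaire is the only source given for it.
- **Content of the instrument.** The same section states: "Credibility and the participant’s expectations of treatment will be evaluated using the Credibility and Expectancy Questionnaire". It divides the six items between two scores: "credibility is derived from the first three thought items, and expectancy derived from the fourth thought question and the two feeling questions".
- **Timing.** "This will be completed at baseline, and at the participant’s second visit with the study physiotherapist (~ 2 weeks post-randomisation". Under Outcome assessment, patient-reported measures are taken at baseline, 6 weeks and 3 months, and "The primary endpoint is 3 months".
- **How participants are blinded.** Study procedures describes limited disclosure: participants know that there are two shoe inserts but "will not be informed of the differences between the two inserts or the study hypotheses". The same section adds: "Secondary outcomes will be self-reported by participants, who are considered assessors".
- **Thresholds and analysis.** Feasibility parameters are set for recruitment, adherence and drop-out, and none for blinding. Under Planned statistical analyses, the feasibility outcomes are reported descriptively.

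**The concern.** The outcome is named for one construct and measured by an instrument for another. A participant can work out which type of insert they were given and still find it credible, especially as the flat insole is presented as a treatment that acts through sensory feedback. A participant who has no idea can rate an insert poorly because it rubs. Similar scores in the two arms therefore do not establish blinding, and different scores do not establish its failure.

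Timing adds to this. The last questionnaire comes at about 2 weeks, while the self-reported outcomes are collected at 6 weeks and 3 months. Whether blinding held until then is not measured.

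At stake is what the full-scale trial can learn. That trial would compare the same two inserts on knee pain and perceived global change, both self-reported. Whether limited disclosure keeps participants unaware is a feasibility question that this study set itself. As written, it could report blinding as successful without having asked anyone what they believed they received.

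**Working it through.** The plan states no figure for blinding (no index, threshold or precision), so there is nothing to reproduce. The check has two parts.

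**1. Construct and timing, set side by side**

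| Needed to judge participant blinding | What the plan provides |
|---|---|
| The participant's belief about allocation | Three credibility items and three expectancy items; 3 + 3 = 6, so no item is left for perceived allocation |
| A reading when the self-reported outcomes are given (6 weeks, 3 months) | Baseline and about 2 weeks |
| Another named source | None. The exit interview covers feasibility, credibility, acceptability and assessment burden, is by invitation, and is not listed as a source for this outcome |

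Study procedures describes baseline measurement before randomisation. The 2-week score therefore appears to be the only one taken after an insert has been fitted.

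**2. Precision, for illustration only**

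The input from the document is 20 per group (Participants section). The case of 16 per group assumes drop-out at the stated 20% limit: 20 × 0.8 = 16. The response patterns are assumptions.

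*Questionnaire scores.* The 95% half-width for a standardised difference between arms is about 1.96 × √(2/n).
- n = 20: 1.96 × √0.100 = 0.62 SD
- n = 16: 1.96 × √0.125 = 0.69 SD

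So even similar observed scores leave sizeable differences in expectancy open.

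*Perceived-allocation item with a don't-know option.* Suppose that 12 of 20 answer correctly, 5 wrongly and 3 don't know.
- Bang index = (12 − 5)/20 = 0.35
- Variance = [0.6 × 0.4 + 0.25 × 0.75 + 2 × 0.6 × 0.25]/20 = 0.7275/20 = 0.0364
- Half-width = 1.96 × √0.0364 = 0.374, so the interval runs from about −0.02 to 0.72

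*Forced guess, half correct.* Exact (Clopper-Pearson) limits for the proportion p are mapped to the index as 2p − 1.
- 10 of 20: 27% to 73%, index −0.46 to 0.46
- 8 of 16: 25% to 75%, index −0.51 to 0.51
- Correct guessing exceeds chance at one-sided p ≤ 0.025 from 15 of 20 (p = 0.021) or 13 of 16 (p = 0.011)

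An added item would thus support a descriptive statement by arm. Only marked unblinding would stand out.

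**The case against.** The best defence is that blinding here works by limited disclosure. Participants are not told that one insert is the comparator, each is fitted with only one type, and the covering fabric is identical. In such a design, equal credibility and expectancy is much of what blinding is meant to secure, and unequal expectancy is a route to both performance and detection bias. That stands. A reader might infer that the questionnaire says nothing about blinding, but the documents do not support so strong a reading. It is indirect evidence, and the fault lies in the label and in any conclusion drawn from it alone.

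Two other inferences also go too far:

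- **Physiotherapists.** A reader might count their lack of blinding as part of this defect. The article says openly that "it is not possible for study physiotherapists to be blinded to group allocation", and success of blinding cannot be judged in people who were never blinded.
- **The blinded assessor.** A reader might ask for this investigator's guesses as well. The clinical outcomes are self-reported, the feasibility outcomes come largely from databases, notes and log books, and the database carries no group identifier. This is a side issue.

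The defence also notes that a guess asked at 3 months can reflect perceived benefit, that careless wording could reveal the withheld hypothesis, and that the estimate would be imprecise. All three hold. They limit the remedy, but they do not make a credibility score a measure of perceived allocation.

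**Conclusion.** The mismatch is real and lies in what the article states, so it is not a detail left to a fuller document. A primary feasibility outcome is tied to an instrument for a different construct, and the last reading falls well before the self-reported outcomes at 6 weeks and 3 months.

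Its weight is moderate. A reader might infer that the trial's results are compromised. They are not: no feasibility threshold depends on blinding, the feasibility outcomes are descriptive, and no treatment-effect estimate changes. What is lost is a supportable answer on blinding for the full-scale trial.

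This rests on the article's description of the questionnaire as complete, and on the questionnaire being the only source for this outcome, as the article lists it. The precision figures rest on the assumed response patterns and on arms of 20 or 16.

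**What to change.** 1. **Relabel.** Report the questionnaire as treatment credibility and expectancy, by arm, and draw no blinding conclusion from it alone.
2. **Add one item at 3 months**, after all patient-reported outcomes are submitted. Ask which type of insert the participant believes they received, with a don't-know option, degree of certainty and reason. The wording must not disclose the contrast or the hypothesis before the item is answered; asking whether they had the insert expected to help more would do so. Answers must still be codable as correct, incorrect or don't know. Ask it before the exit interview and before the post-trial offer of contoured or flat inserts.
3. **Report descriptively** by arm with a 95% confidence interval, for example as a Bang index, alongside the questionnaire scores and the stated reasons.

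**Cost and limits.** One extra item and a minor amendment. Intervals will be wide (half-width about 0.37 to 0.46 with 20 per arm in the cases shown, and about 0.51 for a forced guess with 16). End-of-study guesses can reflect perceived benefit, so the reasons should be read with them.

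**Minimum alternative.** If no item is added, rename the outcome as treatment credibility and expectancy and drop the claim to assess success of blinding.

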#### Secondary outcomes

Secondary outcomes will be collected at baseline, 6 weeks and 3 months.

##### Knee pain severity

Participants will be asked to report their usual and worst pain in the preceding week, as well as pain with a self-nominated aggravating activity. Pain severity will be measured using 100 mm visual analogue scales (where 0 mm = no pain and 100 mm = worse pain imaginable), which have established reliability and validity for PFP [28].

##### Knee injury and Osteoarthritis Outcome Score Child Version (KOOS-Child)

The KOOS-Child assesses five subscales: pain (9 items), symptoms (7 items), difficulty during daily activities (17 items), ability to participate in sport and recreation (7 items), and knee related quality of life (QoL) (6 items) [29]. Participants respond to each question using 5-point Likert scales from 0 (no problems) to 4 (extreme problems). Raw scores are transformed to a 0–100 scale, with 0 representing no knee problems and 100 representing extreme knee problems. KOOS-Child demonstrates good measurement properties in adolescents with knee conditions [30].

##### Knee injury and Osteoarthritis Outcome Score – Patellofemoral subscale (KOOS-PF)

Along with KOOS-Child, participants will complete the KOOS-PF. This subscale was developed for use in people with PFP and patellofemoral osteoarthritis, and designed to be used in conjunction with the five original KOOS subscales [31]. KOOS-PF has 11 items, with identical response and scoring parameters as KOOS-Child (described above). KOOS-PF has adequate measurement properties in adults with PFP [31], although these have not yet been evaluated in adolescents.

##### Global rating of change (GROC)

A 7-point Likert scale will be used to assess GROC at 6 weeks and 12 weeks. Participants will be asked to respond to the question *‘Overall, how has your knee pain changed since the start of the study?’*, using the following responses: ‘completely recovered’, ‘strongly recovered’, ‘slightly recovered’, ‘same’, ‘slightly worse’, ‘much worse’, and ‘worse than ever’. GROC has been used in a previous RCT of adolescents with PFP [7].

##### Patient acceptable symptom state (PASS)

The PASS evaluates the maximum level of symptoms, beyond which the participant considers themselves to be well [32]. Participants will be asked to respond either ‘yes’ or ‘no’ to the following question: *‘Considering all the activities that you do in your daily life, how well you can do these activities, and your level of pain, do you think that your current state is satisfactory?’*

##### Anterior knee pain scale (AKPS)

The AKPS contains 13 items related to current knee symptoms and function [33]. Each item’s response is weighted and summed to produce an overall score between 0 and 100, where 0 represents maximal disability and 100 represents no disability. The AKPS is widely used in studies on PFP, and has established reliability and validity in adults with PFP [28].

##### Youth quality of life – short form (YQOL-SF)

The YQOL-SF is a generic assessment of quality of life in individuals aged 11–18 years with and without chronic disease or disability [34]. YQoL-SF version 2 consists of 15 items derived from the perceptual instrument of the YQOL-R, and assess aspects of sense of self, social relationships, environment and general quality of life. Participants respond to each item on a scale from 0 (not at all) to 10 (completely or a great deal). Overall transformed scores range from 0 to 100, where the higher score represents better quality of life.

##### EuroQol-5D-5L

The EQ-5D (EuroQoL) questionnaire is a generic measure of health-related quality of life, comprised of five items covering five dimensions: (i) mobility; (ii) self-care; (iii) usual activities; (iv) pain/discomfort; and (v) anxiety/depression [35]. Participants will complete the 5 L version, where each subscale has five possible responses. Participants will also complete a visual analogue scale for self-reported health state, where 0 represents worst imaginable health state and 100 represents the best imaginable health state. We elected to use the adult version of EQ-5D-5L for this study, rather than the youth version, as some of our participants will fall outside the recommended age group for the EQ-5D-Y (age 8–15 years), and to facilitate comparison with data collected in previous studies in adolescents with PFP [7].

##### Use of co-interventions

Participants will be asked to keep a daily record of any use of co-interventions, outside their allocated intervention, utilized throughout the study (e.g. pain medication, physiotherapy, knee brace, other footwear interventions). This will be recorded in their log books over the three-month study period.

### Data management

Each participant’s information will be coded in a re-identifiable format, and stored in a database with no group identifier to maintain blinding of the investigator. Electronic databases containing participant contact details will be password protected. All databases will be stored on a password protected computer. All hard copies of data will be coded and stored in a locked filing cabinet in the School of Health and Rehabilitation Sciences at The University of Queensland.

### Planned statistical analyses

Descriptive statistics will be calculated for the primary feasibility outcomes. Estimates of i) standard deviation of the secondary clinical outcomes, and ii) between-group differences in secondary clinical outcomes, with accompanying 95% confidence intervals, will be calculated.

### Post-trial care

If participants experience any adverse events after completion of the study, they will be referred for follow up by appropriate health care providers. Participants will be permitted to keep their intervention after completion. On request, participants will be provided with additional shoe inserts on completion of the study (either contoured or flat shoe inserts). The contact details of the primary investigator will be available to each participant for any concerns related to the study.

### Study exit interview

After study completion, participants will be invited to partake in a one-on-one semi-structured exit interview. Questions will be aimed at further exploring aspects of study feasibility, and credibility and acceptability of the interventions, and burden of assessment schedule. Interviews will be conducted by the blinded investigator ([name]).

### Distribution of results

Once completed, study outcomes will be made available to participants via email or post on request. Outcomes will be disseminated via peer-reviewed publications, and submission of abstracts to appropriate national and international conferences.

## Discussion

PFP in adolescents is a problem, with clear implications for function, quality of life, and future knee health. Current clinical guidelines for PFP management are largely based on studies conducted in adults with PFP, with minimal data available regarding efficacious treatments for adolescents with PFP. Given the significance and potential impact of PFP in adolescents, it is imperative that we identify interventions that are acceptable and effective for this specific population. This feasibility study is the first step in evaluating foot orthoses as an intervention for adolescents with PFP.

We chose to evaluate prefabricated foot orthoses rather than custom foot orthoses in adolescents with PFP. This was based on the greater accessibility and substantially lower costs associated with prefabricated orthoses compared to custom orthoses [36]. Eng & Pierrynowski [8] evaluated the effect of medially posted soft foot orthoses in 20 adolescent females with bilateral PFP (mean ± SD age 15 ± 1 years, range 13–17 years). Participants were randomized to either posted or flat insoles, with both groups receiving an exercise program. After 8 weeks, the group who received medially posted orthoses had significantly greater improvements in pain severity during running, stair ambulation and squatting, compared to the group who received flat insoles. Notably, significant between-group differences at 8 weeks tended to exceed the minimal clinically important difference for pain measured on a visual analogue scale (2 cm) [28]. While this study provides important preliminary information regarding the potential effects of foot orthoses for adolescents with PFP, there have been no further RCTs in this area since 1993. Furthermore, the soft foot orthosis prescription used in the study by Eng and Pierrynowski [8] likely does not reflect current prescription practices [17]. Together, this highlights the need for further studies in order to support the use of foot orthoses in adolescents with PFP.

Many adolescents experience bilateral symptoms (70% versus 43% in adults) [37]. Foot orthoses are typically worn bilaterally, and thus have potential effects on both lower limbs during weight bearing activities. This is important for PFP, in that most aggravating activities involve weight bearing. Furthermore, because foot orthoses can be worn during physical activity and exercise (including therapeutic exercise), they may play a role in relieving pain and facilitating participation. Importantly, the use of a passive intervention such as foot orthoses may help to overcome issues with treatment adherence, which can be a substantial barrier in adolescents. Foot orthoses require minimal time or cost in that they are worn in everyday footwear, and easily transferred from school shoes to sports shoes. They have minimal side effects (e.g. rubbing and blistering), and in the case that they do, can be adjusted to enhance comfort [12].

This feasibility study is an important initial step in evaluating the efficacy of foot orthoses for adolescents with PFP, and has a number of strengths. The study design adheres to the SPIRIT guidelines [18] and CONSORT extension for pilot and feasibility studies [19]. Key features of the study design include randomisation, concealed allocation, and blinded data collection and analysis. The interventions to be evaluated in this study are simple to replicate in clinical practice, and are being administered in the clinical setting by physiotherapists. Secondary outcome measures that will provide estimates of treatment effects have been selected based on their applicability for use in adolescents, as well as their established measurement properties in PFP and, where possible, adolescents.

## Conclusion

HAPPi Kneecaps! will determine the feasibility of conducting a full-scale RCT evaluating the effects of foot orthoses on knee pain severity and patient-perceived global change, compared to flat insoles, in adolescents with PFP. Secondary outcomes will provide estimates of treatment effect sizes for prefabricated foot orthoses, compared to flat insoles, in this population. Given the high prevalence and burden of PFP in adolescence, and potential long-term sequelae, this study is an important first step in identifying appropriate and efficacious interventions for this population.

## Data Availability

De-identified individual participant data will be collected during the trial. Access to this data will be determined on a case-by-case basis at the discretion of the Principal Investigator, after publication of the study, with a requirement to sign a data access agreement.

## Abbreviations

AKPS: Anterior Knee Pain Scale
CONSORT: Consolidated Standards of Reporting Trials
EQ-5D: EuroQol-5D
EVA: Ethylene-vinyl acetate
GROC: Global Rating of Change
KOOS: Knee injury and Osteoarthritis Outcome Score
KOOS-PF: Knee injury and Osteoarthritis Outcome Score – Patellofemoral Subscale
PASS: Patient Acceptable Symptom State
PFP: Patellofemoral pain
RCT: Randomised controlled trial
SPIRIT: Standard Protocol Items: Recommendations for Interventional Trials
YQoL-SF: Youth Quality of Life – Short Form
